##### Functional fall risk assessments

Additionally to the SPPB [24] and usual GS [25, 26] assessed exactly as described in part I, the Timed up and Go test (TUG) [38, 45] will be assessed. The time to complete the test at the usual GS will be recorded in seconds [45]. The hand-grip strength will be evaluated with a Jamar dynamometer with participants sitting on a chair, their elbow in 90° flexion with the forearm resting in a neutral position on the arm of a chair and the wrist in 0–30° dorsiflexion [40]. The strength will be evaluated in kg [40].

##### Index and reference test assessment

A health care professional/assessor, blinded for the test results of the functional fall risk assessments and the fall history of the participants, will measure participants’ HAS following the testing procedure described for the index test. The strength values will be entered in the e-CRF.

During the follow-up phase of 12 months, participants will be asked to complete fall diaries as soon as they experienced a fall. The study nurse additionally will call participants every 6 months.

#### Sample size calculation

According to our previous findings of the AUC of hip abductors strength in a standing position, good AUC values (0.85) are expected [16, 43] with a 95 % confidence interval not going below 0.7 [16]. Using the statistical environment R [31] with a significance level of 5 % and a power of 80 % we need 31 positive and 104 negative cases for the evaluation of the diagnostic accuracy (criterion validity). Compensating for an expected drop-out rate of 20 % over the 12 months follow up period, we will have to include 169 participants. As the sample size calculation for the construct validity is smaller than for the criterion validity we base our study on the sample size for the criterion validity.

#### Data analysis

Data analyses will be performed with SPSS version 25 (IBM Corp. Released 2017. Armonk, NY: IBM Corp.). Descriptive statistics for the sample characteristics and the functional and non-functional fall related variables will be performed. For continuous variables, the mean and standard deviation (mean ± SD) will be presented.

The definition of the evaluation of the MVIS and RFG of the HAS is described in our previous article [15]. MVIS and RFG will be normalized to body weight [16].

For the construct validity, the correlations of the HAS (MVIS and RFG) with the functional fall risk assessments SPPB, TUG, GS, and HGS will be presented.

For the criterion validity, the AUC and the diagnostic values of HAS, TUG, SPPB, GS, and HGS, compared to the chosen external criterion, history of falls, and 12 months fall prediction (sensitivity, specificity, PPV, NPV, LR+, and LR-) as well as cut-off values will be presented. We will further calculate the net sensitivity and net specificity to present the additional use of HAS in a test battery with other fall risk assessments (SPPB, TUG, gait speed). Additionally we will calculate indices for calibration and discrimination.

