#### Study aims and hypotheses

For the evaluation of construct validity of the hip abductors’ strength measurement, we will compare the hip abductors strength to other currently used functional fall risk assessments like the SPPB [24], TUG [38], GS [25], and HGS [40]. We aim to assess the strength and direction of the correlation between currently used fall risk assessments SPPB, TUG, GS, and HGS with the hip abductors strength, each separately. We hypothesize to find moderate [42] positive correlations (0.40–0.69) between hip abductors strength, SPPB, GS, and HGS and moderate negative correlations between the TUG and hip abductors strength. We are expecting moderate correlations as HAS assesses the same construct but not completely the same parameters as the other fall risk assessments. SPPB and TUG, and in some ways GS, include the assessment of functional parameters like gait and balance, whereas HGS and HAS assessment include only strength. We expect the correlations between hip abductors, SPPB, GS, and HGS to be positive and hypothesize to find the highest –correlation (close to the upper boundary of a moderate correlation ≤ 0.69) between SPPB and HAS as both include a specific strength assessment of the lower limb. The correlation between HGS and HAS is expected to be rather close to the lower boundary of a moderate correlation (≥ 0.4) as they don’t assess the strength of the same body parts. The correlation between the TUG and HAS is hypothesized to be almost as strong as between the SPPB and HAS but due to the scoring of the TUG in a negative direction.

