The criterion validity will be evaluated considering HAS as the index test and fall history of the last 6 months as well as falls during the follow-up time of 12 months as the predefined reference standard. We intend to evaluate if hip abductors’ strength assessed with the new procedure is a good diagnostic tool to classify older persons into fallers and non-fallers and/or can improve fall risk detection by combining it with other functional fall risk assessments. Therefore, for the criterion validity we aim to investigate the diagnostic accuracy of HAS (MVIS and RFG), by evaluating its area under the curve [AUC], sensitivity [sens], specificity [spec], positive predictive value [PPV], negative predictive value [NPV], and positive and negative likelihood ratio [LR+, LR-] and the respective, clinically relevant cut-off values. We will compare these values, in the same population, with the indicators of diagnostic accuracy for TUG, SPPB, GS and HGS. We will further calculate net sensitivity and specificity of HAS to get insight in its possible combination with our chosen fall risk assessments (TUG, SPPB, GS and HGS). We hypothesize to find a good diagnostic accuracy of HAS assessed with the new procedure and AUC values of ≥ 0.85 [16, 43] with a 95 % confidence interval not going below a moderately accurate level of 0.7 [16, 44]. The diagnostic accuracy will be comparable to that of the fall risk assessments TUG, SPPB and GS and has a better accuracy than HGS. Additionally we expect a high accuracy of HAS in recognizing fallers in parallel testing with TUG, SPPB, GS, and HGS [17].

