##### Socio-demographic data and fall risk assessment

As for part I, the reliability part, the socio-demographic data (age, sex, height, and weight) will be obtained by a phone call or from the electronic participant record of the AFFIRM-CT study. A variety of non-functional fall risk related variables for the description of our participants will be assessed. The fall history of the last 6 months and the MMSE [28] will be evaluated by the study nurse exactly as described in the data collection section of part I of this protocol. The number and names of the medication the participants take will be written down on the participant’s documents to get an indication of their poly-medication. Further, participants’ physical activity level, assessed with a physical activity tracker worn on the wrist over a time span of 7 days, and the use of walking aids/assistive devices will be registered in the e-CRF.

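### HAS is weight-normalised and hand-grip strength is not, as far as the article says, so the HAS–HGS correlation and accuracy comparison need a pre-specified matched-scale version

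*Protocol article*

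**What the plan says.** - **HAS scaling.** Part II, Data analysis: "MVIS and RFG will be normalized to body weight [16".
- **HGS scaling.** Part II, Functional fall risk assessments, says of hand grip: "The strength will be evaluated in kg [40". No section divides HGS by weight or adjusts it for weight.
- **Correlation analysis.** Part II, Data analysis: "the correlations of the HAS (MVIS and RFG) with the functional fall risk assessments SPPB, TUG, GS, and HGS will be presented".
- **Construct hypothesis.** Part II, Study aims and hypotheses: "The correlation between HGS and HAS is expected to be rather close to the lower boundary of a moderate correlation", with that boundary given as 0.4. The same paragraph separates the two measures from the gait and balance tests, "whereas HGS and HAS assessment include only strength", and gives the different body parts as the reason for the modest expected value.
- **Accuracy hypothesis.** The same section expects that HAS "has a better accuracy than HGS".

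**The concern.** HGS is the one comparator that the plan treats as the same kind of quantity as HAS: strength and nothing else. Once HAS is divided by weight, it becomes relative strength. Grip as recorded is absolute strength. If heavier people tend to have a stronger grip, dividing HAS by weight lowers HAS in the people whose grip is high, and the HAS–HGS correlation falls for a reason unrelated to which muscles are tested.

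Two stated hypotheses are touched. A HAS–HGS correlation below 0.4 could come from the one-sided denominator, where the protocol would look to body region. A HAS lead over HGS in accuracy could come from weight adjustment, with nothing gained from testing the hip abductors.

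**Working it through.** **The plan's own figure.** The only calculated size in Part II is the sample size. A test of AUC 0.85 against 0.70 with 31 fallers and 104 non-fallers has 79.7% power (two-sided 5%, Hanley–McNeil variance), and 135/0.80 = 168.75, rounded up to 169. HGS scaling plays no part in this, and the figure stands.

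**Inputs for the scaling check.** The protocol gives no SDs and no correlations with weight, so all of these are assumptions:
- CV of HAS, h = 0.30–0.40
- CV of HGS, g = 0.30–0.35
- CV of weight, b = 0.15–0.18
- correlations of HAS and HGS with weight, r_HB and r_GB = 0.2–0.5, varied independently
- absolute-scale HAS–HGS correlation, r = 0.50 or 0.40

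**Formulas (log scale).**
- Only HAS divided by weight: (r·h − r_GB·b) / √(h² + b² − 2·r_HB·h·b). The CV of HGS cancels.
- Both divided: (r·h·g − r_HB·h·b − r_GB·g·b + b²) / [√(h² + b² − 2·r_HB·h·b) · √(g² + b² − 2·r_GB·g·b)].

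**Worked example** (h = g = 0.30, b = 0.18, both weight correlations 0.3, r = 0.50).
- Only HAS divided: (0.150 − 0.054) / √(0.09 + 0.0324 − 0.0324) = 0.096/0.30 = 0.32.
- Both divided: (0.045 − 0.0162 − 0.0162 + 0.0324)/0.09 = 0.50.
- Weight-adjusted partial correlation: (0.50 − 0.09)/(1 − 0.09) = 0.45.

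**Range when only HAS is divided.**

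| Absolute r | Lowest (h 0.30, b 0.18, r_HB 0.2, r_GB 0.5) | Highest (h 0.40, b 0.15, r_HB 0.5, r_GB 0.2) |
|---|---|---|
| 0.50 | (0.150 − 0.090)/√0.1008 = 0.19 | (0.200 − 0.030)/√0.1225 = 0.49 |
| 0.40 | (0.120 − 0.090)/√0.1008 = 0.09 | (0.160 − 0.030)/√0.1225 = 0.37 |

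Every value lies below its absolute-scale starting point. With both divided, r = 0.50 becomes 0.32–0.55 over the same grid.

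**The shared-denominator artefact.** With r = 0, no weight correlations and CVs 0.30/0.30/0.18, the both-divided correlation is 0.0324/(0.09 + 0.0324) = 0.26. It arises only because both numbers share a divisor.

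**AUC.** Assume two equally informative strength measures (CV 0.30), weight CV 0.15–0.20, strength–weight correlation 0–0.6, and AUC 0.85 on the scale that falls follow. The AUC on the other scale is Φ(ρ·Φ⁻¹(0.85)), where ρ is the correlation between log strength and log strength-per-weight.
- Weight CV 0.15, correlation 0: ρ = 0.09/√(0.09 × 0.1125) = 0.894, AUC 0.823.
- Weight CV 0.20, correlation 0.6: ρ = 0.054/√(0.09 × 0.058) = 0.747, AUC 0.781.

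The gap is therefore about 0.03–0.07. It favours the weight-normalised measure if falls follow relative strength and the absolute measure if falls follow absolute strength. For scale, the standard error of the HAS AUC at 31 + 104 is about 0.045.

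**The case against.** Several stronger readings are tempting, and the document does not support them.

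- **That the plan rules out scaling HGS.** It does not say so. The kg statement is a unit of measurement in a data-collection section, and a fuller document might scale grip. What stands is that the analysis section does specify scaling, for HAS alone, and then names HGS in the next two paragraphs.
- **That unlike scales are an error in themselves.** They are not. HAS is also compared with seconds, points and walking speed, and an AUC does not depend on units. Asking whether weight-normalised HAS classifies fallers better than grip as recorded is a legitimate clinical question. It is a different question from whether the hip abductors add information.
- **That the scaling will make the 0.4 hypothesis fail.** This cannot be inferred. The expected value may already refer to normalised HAS, every input above is assumed, and from 0.50 part of the range stays above 0.40. The protocol attaches no pass/fail decision to the correlations, and at 135 participants the 95% interval around 0.40 is about 0.25–0.53.
- **That the comparison is tilted towards HAS.** The direction depends on whether falls follow relative or absolute strength, which the document does not settle.
- **That dividing both by weight is a clean cure.** It is not, because the shared denominator can inflate the correlation.

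What survives is narrower. The protocol reasons about two pure strength measures that differ by body part, and the analysis as written adds a second difference between them.

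**Conclusion.** The point holds in limited form. Weight adjustment of one strength measure only, as far as the article states, mixes body size into a correlation that the protocol interprets by body region, and into an accuracy comparison between two strength tests. Under the assumed inputs the loss in correlation runs from negligible (0.50 to 0.49) to large (0.50 to 0.19). The possible AUC shift is about 0.03–0.07 in either direction. These are illustrations and not predictions for this cohort. One of four construct correlations and one accuracy comparison are affected; the sample size and the main HAS AUC target are not. Severity is minor to moderate: a cheap improvement in what two stated hypotheses can show.

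**What to change.** In Part II, Data analysis:
1. State how HGS is scaled.
2. Pre-specify that the HAS–HGS correlation and the HAS versus HGS accuracy comparison are also reported on matched scales: both absolute, and both per kg body weight. For the correlation, a weight-adjusted partial correlation is an alternative.
3. Name in advance the matched-scale result on which the HAS–HGS hypothesis is judged. The matched versions can differ among themselves, so choosing after seeing the data could decide whether 0.4 is reached.
4. Keep the comparison against HGS in kg, labelled as the comparison of the two tests as used.

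The cost is a sentence or two and a little extra analysis. No new data are needed, since the sociodemographic data, weight included, "will be obtained by a phone call or from the electronic participant record of the AFFIRM-CT study". The both-per-weight correlation should carry a caution that a shared denominator can inflate it.

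### HAS cut-offs will be chosen and judged in the same small Part II sample, so sensitivity, specificity and the values built on them will be somewhat optimistic

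*Protocol article*

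**What the plan says.** - **Cut-offs are an output.** Part II, Study aims and hypotheses, lists AUC, sensitivity, specificity, predictive values and likelihood ratios for HAS (MVIS and RFG), "and the respective, clinically relevant cut-off values". Part II, Data analysis, repeats this for HAS, TUG, SPPB, GS and HGS: "sensitivity, specificity, PPV, NPV, LR+, and LR-) as well as cut-off values will be presented". It then adds net sensitivity and net specificity for HAS within a test battery.
- **There is one sample.** Part II, Sample size calculation: "we need 31 positive and 104 negative cases", raised to 169 for an "expected drop-out rate of 20 % over the 12 months follow up period". No second sample, hold-out or resampling is mentioned for Part II. In Part I, bootstrapping is specified for the ICC confidence intervals.
- **There is no evident outside source for a HAS cut-off.** The Discussion says no articles on closed-chain HAS are available yet. The sample size section cites earlier AUC findings for a standing position but names no cut-off.
- **Calibration** is a single sentence: "Additionally we will calculate indices for calibration and discrimination". It names no model and no index.

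**The concern.** A threshold tuned to a sample fits that sample's chance features as well as the real separation between fallers and non-fallers. Accuracy counted at that threshold in the same people is biased upwards on average, and the bias is larger when the smaller group, here the fallers, is small.

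Sensitivity, likelihood ratios and cut-offs are the figures a clinician would apply, and the article says the clinimetric results will show whether HAS measurement should be encouraged in fall risk assessment. It also expects HAS to be comparable with TUG, SPPB and GS and better than HGS. If those tests are read at established cut-offs and HAS at a tuned one, only HAS gets the optimism. If all are tuned, all are inflated. The net values for combined testing are built from the single-test values and carry the bias on.

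**Working it through.** **1. The plan's own sample size.** Inputs from Part II, Sample size calculation: "good AUC values (0.85) are expected", "confidence interval not going below 0.7", "with a significance level of 5 % and a power of 80" per cent, and 31 and 104 cases (ratio k = 104/31 = 3.355). I test AUC 0.85 against 0.70, two-sided, with the large-sample Hanley-McNeil variance.

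- Per faller, V(A) = (A/(2−A) − A²)/k + (2A²/(1+A) − A²).
- V(0.70) = (0.5385 − 0.4900)/3.355 + (0.5765 − 0.4900) = 0.1009.
- V(0.85) = (0.7391 − 0.7225)/3.355 + (0.7811 − 0.7225) = 0.0635.
- Fallers needed = (1.96·√0.1009 + 0.8416·√0.0635)² / 0.15² = 30.97, so 31.
- 31 + 104 = 135, and 135/(1 − 0.20) = 168.75, so 169.

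The stated size reproduces and is not in dispute. It fixes the setting: about 31 fallers and 104 non-fallers.

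**2. Optimism at a data-chosen cut-off.** My assumptions are equal-variance normal scores in fallers and non-fallers, and a cut-off that maximises sensitivity plus specificity (Youden). The article names no rule. There are 20,000 simulated studies per setting. True performance at each chosen cut-off comes from the known distributions.

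| True AUC | Fallers / non-fallers | Apparent sens / spec | True sens / spec | Excess sens | Excess spec | Excess sum |
|---|---|---|---|---|---|---|
| 0.70 | 31/104 | 0.699 / 0.666 | 0.625 / 0.644 | 0.074 | 0.022 | 0.096 |
| 0.80 | 31/104 | 0.769 / 0.743 | 0.704 / 0.724 | 0.065 | 0.019 | 0.084 |
| 0.85 | 31/104 | 0.810 / 0.784 | 0.750 / 0.767 | 0.060 | 0.017 | 0.078 |
| 0.90 | 31/104 | 0.855 / 0.832 | 0.801 / 0.817 | 0.054 | 0.016 | 0.070 |
| 0.85 | 39/130 | 0.806 / 0.781 | 0.753 / 0.766 | 0.053 | 0.015 | 0.068 |
| 0.85 | 45/90 | 0.807 / 0.780 | 0.762 / 0.757 | 0.045 | 0.023 | 0.067 |

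At AUC 0.85 and 31/104 the apparent sum exceeds the true sum in 85% of studies. Having no drop-out (39/130) or more fallers (45/90) reduces the bias only a little.

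**3. What follows for the derived values**, from the average pairs at AUC 0.85 and 31/104:

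- LR+: 0.810/(1 − 0.784) = 3.75 apparent, 0.750/(1 − 0.767) = 3.22 true.
- LR−: 0.190/0.784 = 0.24 apparent, 0.250/0.767 = 0.33 true.
- Fallers missed: 19% apparent, 25% true.
- PPV at prevalence 31/135 = 0.230: 0.810·0.230/(0.810·0.230 + 0.216·0.770) = 0.53 apparent, 0.750·0.230/(0.750·0.230 + 0.233·0.770) = 0.49 true.

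**4. The AUC of the single test.** In the same simulation its mean is 0.851 for a true 0.85. It uses no cut-off and is not inflated.

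**5. Calibration, if a logistic model is fitted.** In 1,500 simulated one-predictor fits, intercept and slope on the fitting data were 0 and 1 every time, as maximum likelihood requires. A ten-group Hosmer-Lemeshow test on the same data rejected in 5.4% of studies when the model was right and in 17.4% when its form was wrong.

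**The case against.** The strongest reply is that this rests on silence. The article says only that accuracy values and cut-offs will be presented. The cut-off rule and any internal validation are details that a condensed article may leave to the full protocol or analysis plan, neither of which is shown. That stands as a limit: the article does not prove that no correction is planned. It does not remove the point, because the article does state that cut-offs are an output reported with accuracy from one sample, and carrying that out as written gives optimistic figures.

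The reply can also say that the size depends on the Youden rule, that a clinically relevant cut-off could be set another way (for example at a target sensitivity) with different optimism, and that 0.06 is less than one standard error of sensitivity with 31 fallers, √(0.75·0.25/31) = 0.078. All of this is fair. But sampling error is shown by a confidence interval and goes either way, whereas this bias has a direction and an ordinary interval around the apparent value does not reveal it.

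A reader might infer three stronger things that the document does not support:

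- **That every cut-off is tuned to this sample.** TUG, SPPB, GS and HGS are tests in current use, and the article does not say where their cut-offs come from.
- **That the calibration result cannot fail.** No model or index is named. Only the intercept and slope of a logistic model on its own fitting data are fixed. Other indices can show misfit.
- **That the AUC is inflated too.** For a single test it is not. Only the AUC of a fitted combination would be.

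**Conclusion.** The point holds for the HAS cut-offs and for the values reported at them: sensitivity, specificity, predictive values, likelihood ratios and net values. Under the assumptions in the working, sensitivity is overstated by about 0.06 and specificity by just under 0.02, a sum of 0.08 (0.07 to 0.10 for true AUCs from 0.90 to 0.70). That HAS cut-offs come from this sample is an inference, but the document offers no other source. The comparison is tilted towards HAS only if the comparators keep established cut-offs.

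The main hypothesis (AUC of at least 0.85 with a lower limit not below 0.7) and the sample size are untouched. The calibration point is conditional on a logistic or combined model being fitted. This is a modest, inexpensive improvement to the analysis and not a flaw in the design.

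**What to change.** In Part II, Data analysis:

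- State the rule by which the HAS cut-offs (MVIS and RFG) are chosen, and say for each comparator whether its cut-off is pre-existing or derived from these data.
- Repeat the cut-off choice in every bootstrap resample (for example 1,000) and subtract the average optimism. Report corrected sensitivity, specificity, predictive values, likelihood ratios and net values for HAS and for any comparator with a data-derived cut-off. Label the uncorrected values as apparent.
- If a logistic or combined model is fitted, repeat the fit in the resamples and report its AUC and calibration slope corrected as well. The AUC of a single test needs no such correction.

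This needs no further participants or data. The cost is some programming and slightly less favourable accuracy figures. The correction is partial: in a check at 31/104 and AUC 0.85, bootstrapping brought average sensitivity from 0.81 to 0.77, against a true value of about 0.75. The corrected cut-offs would still need confirmation in a separate sample.

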## Discussion

The detection of persons at risk of falls is a major public health concern and should have high priority. Unfortunately, the diagnostic accuracy of currently used functional tests (e.g. SPPB and TUG) to assess older persons’ fall risks remains moderate and additionally, those tests usually don’t reveal directly targetable parameters for the prevention or rehabilitation of persons at risk. Amongst others, this led to the development of the above-mentioned adapted measurement instrument for hip abductors strength of older persons aged 65 years and over. Understanding the construct of older persons’ fall risk might benefit from the additional assessment of HAS as it is evaluating a complementary aspect of falls [17]. To perform several tests either in parallel or serial testing increases the certainty of detecting as many persons at risk of falls (true positives or true negatives) as possible (increase in net sensitivity and/or net specificity). As we know that the diagnostic accuracy of currently used functional fall risk assessments is only moderate, we are interested to investigate if HAS could improve a reliable and valid fall risk detection by its use in a test battery. Compared to the currently used functional performance tests to detect the fall risk (e.g. SPPB, TUG) HAS might be a directly targetable fall-risk parameter, which could contribute to treatment goal setting and might also to a well-targeted treatment (to be proven in future studies).

As there are not yet any articles available using the parameter hip abductors strength in a closed chain position, we need to investigate its clinimetric properties before a wide implementation can be considered. We will investigate this in a population of older adults with no additional diseases known to increase the fall risk. However, many diseases are known to increase the fall risk (e.g. neurological diseases) and future studies might investigate the additional use of the assessment of hip abductors strength for the assessment and treatment of these persons when reliability and validity are proven and acceptable in this study.

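### A gain in net sensitivity or net specificity does not show that HAS adds information; the parallel-testing hypothesis needs a comparison of each existing test with and without HAS

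*Protocol article*

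**What the plan says.** Under Part II, Study aims and hypotheses, the protocol article sets the aim of learning whether HAS sorts older people into fallers and non-fallers and whether it improves detection alongside other functional tests. For the combination it says: "We will further calculate net sensitivity and specificity of HAS to get insight in its possible combination with our chosen fall risk assessments". The four tests named there are TUG, SPPB, gait speed (GS) and hand grip strength (HGS). The only hypothesis on combined testing is: "Additionally we expect a high accuracy of HAS in recognizing fallers in parallel testing with TUG, SPPB, GS, and HGS".

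Part II, Data analysis, repeats the measure: the plan is to "calculate the net sensitivity and net specificity to present the additional use of HAS in a test battery with other fall risk assessments". The tests listed there are SPPB, TUG and gait speed, without HGS. The section closes with "Additionally we will calculate indices for calibration and discrimination".

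The Discussion gives the rationale: "To perform several tests either in parallel or serial testing increases the certainty of detecting as many persons at risk of falls". In brackets it describes the benefit as a rise in one or both of the net values.

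The hypothesis for HAS as a single test, by contrast, has numbers: under Sample size calculation, "good AUC values (0.85) are expected", with a lower confidence limit of at least 0.7.

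**The concern.** Net sensitivity and net specificity under a parallel or serial rule move in directions fixed by the rule, whatever test is added. With an either-positive rule, every faller already detected stays detected, so net sensitivity cannot fall. Every non-faller already called positive stays positive, so net specificity cannot rise. A both-positive rule does the opposite. One of the two values is thus guaranteed not to get worse, and the Discussion counts a rise in either as the benefit.

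The combination hypothesis leans on the value that cannot get worse under parallel testing, namely recognition of fallers. It does not say how high is high, does not compare with the existing test alone, and does not say how much specificity may be lost. At stake is the answer to a stated aim: a report that adding HAS in parallel found more fallers would be literally true and would not show that HAS carries information beyond TUG, SPPB, GS or HGS.

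**Working it through.** **Plan's own figures.** The article gives no figure for net sensitivity or net specificity. Its sample size, 31 fallers plus 104 non-fallers = 135, and 135 / 0.80 = 168.75, rounded up to 169, is for the single-test AUC and is not affected by this point.

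**Inputs.** The 31 fallers and 104 non-fallers come from Part II, Sample size calculation. The article gives no sensitivity (Se) or specificity (Sp) for any test, so the following are assumptions: existing test Se 0.60 to 0.90 and Sp 0.60 to 0.75; an informative HAS with Se 0.80 and Sp 0.75; an uninformative test (coin toss) with 0.50 and 0.50. Errors are taken as independent within fallers and within non-fallers, for illustration only.

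**Formulas.**
- Parallel: net Se = 1 − (1 − Se1)(1 − Se2); net Sp = Sp1 × Sp2.
- Serial: net Se = Se1 × Se2; net Sp = 1 − (1 − Sp1)(1 − Sp2).
- Youden's J = Se + Sp − 1; LR+ = Se / (1 − Sp).

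**Coin toss added to 0.70/0.70.**
- Parallel: net Se = 1 − 0.30 × 0.50 = 0.85; net Sp = 0.70 × 0.50 = 0.35. J goes from 0.40 to 0.20 and LR+ from 0.70/0.30 = 2.33 to 0.85/0.65 = 1.31.
- Serial: net Se = 0.35; net Sp = 1 − 0.30 × 0.50 = 0.85.

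So an uninformative test raises net sensitivity under one rule and net specificity under the other.

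**Parallel rule over the assumed range.**

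| Existing test Se/Sp (J) | plus coin toss: net Se/Sp (J) | plus informative HAS: net Se/Sp (J) |
|---|---|---|
| 0.60/0.70 (0.30) | 0.80/0.35 (0.15) | 0.92/0.525 (0.445) |
| 0.70/0.70 (0.40) | 0.85/0.35 (0.20) | 0.94/0.525 (0.465) |
| 0.80/0.75 (0.55) | 0.90/0.375 (0.275) | 0.96/0.562 (0.522) |
| 0.90/0.60 (0.50) | 0.95/0.30 (0.25) | 0.98/0.45 (0.43) |

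In every row both added tests raise net Se and lower net Sp. The direction of change does not separate them; only the exchange between the two values does. Even J is not a clean arbiter: the informative HAS lowers it in the last two rows, because an either-positive rule at fixed cut-offs can waste information that a model would use.

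**At the planned size.** With 31 fallers, existing Se 0.70 and a coin toss in parallel, net Se stays unchanged only if the coin finds no extra faller: (1 − 0.30 × 0.50)^31 = 0.85^31, about 0.6%. In 20,000 simulated samples it rose in 99.4%, was unchanged in 0.6% and never fell; net Sp among 104 non-fallers fell in all of them.

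**Had the hypothesis set a threshold.** For that same coin-toss battery (true net Se 0.85, 31 fallers), the observed net Se would reach 0.80, 0.85, 0.90 or 0.95 in about 83%, 49%, 30% and 4% of samples.

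**Dependence between tests.** The article expects HAS to correlate moderately with the comparators ("We are expecting moderate correlations as HAS assesses the same construct"). It does not say how net values will be computed. For two tests each at an assumed 0.80/0.70, the product formulas above give 0.96/0.49, whereas two tests that classify everyone identically give 0.80/0.70. Counting joint results avoids having to assume where between these the tests lie.

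**The case against.** The strongest reply is that the plan does not rely on net sensitivity alone. Aims and Data analysis both name net specificity, and for a coin toss that value halves. This stands. A reader might infer that the planned measure will favour HAS whatever the data show; the documents do not support that, because the planned pair would expose an uninformative test to anyone who reads both values.

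Second, the hypothesis is one of high accuracy, not of a gain. A reader might infer that it cannot fail as a matter of arithmetic. That is also unsupported: net sensitivity can stay flat if HAS finds no extra faller, and a stated threshold could be missed, as the 30% and 4% figures show. The fault is that no threshold is stated.

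Third, a reader might infer that the net values will be biased by an independence formula and take the hypothesised correlations of 0.40 to 0.69 as its size. The article states no formula, all tests are done on the same participants so joint counting is possible, and those correlations are for the whole sample, not within fallers and non-fallers. No size of bias can be read from them.

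Fourth, the calibration and discrimination indices may be specified in a fuller document, and the aim is worded as gaining insight. Their lack of detail is therefore not held against the article. But the article itself chose the net values as the way to present the added use of HAS and worded the hypothesis, and no current passage ties the other indices to a battery with and without HAS.

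**Conclusion.** The point holds in a limited form. A gain in net sensitivity under parallel testing, or in net specificity under serial testing, is not evidence of added value, because a non-negative change is built into the rule. Reporting both values reveals the trade-off but does not settle whether HAS adds information: no passage says how a gain in one is weighed against a loss in the other, and the hypothesis considers fallers only, with no threshold, no comparator and no specificity limit.

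The direction of the changes is exact and needs no assumption. The size is illustrative: 70%/70% becoming 85%/35% with a coin toss rests on assumed accuracies and on the coin being independent of the existing test. The single-test AUC analysis and the sample size are untouched. This is a cheap improvement to a secondary aim, worth making before analysis; it does not threaten the main design.

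**What to change.** 1. For each comparator (TUG, SPPB, GS, HGS), fit two logistic models for falls over the 12-month follow-up: comparator alone, and comparator plus HAS, both as continuous variables. Take as the measure of added value the likelihood-ratio test for HAS and the bootstrap optimism-corrected change in AUC with its confidence interval.
2. Keep net sensitivity and net specificity as description, always shown as a pair next to the values of the existing test alone, and counted from each participant's joint results.
3. Reword the combination hypothesis under Part II, Study aims and hypotheses, so that it states an improvement over the comparator alone on that measure.
4. Remove from the Discussion the suggestion that a rise in either net value is in itself the benefit, and align the test lists: HGS is among the combinations in the aims but absent from the list in Data analysis.

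The cost is a few regressions on data already collected: four comparators and two HAS measures (MVIS and RFG) make eight model pairs. No extra participants or visits are needed. The limit is precision: with about 31 fallers the intervals for the change in AUC may be wide, so the results should be read as estimates, and a non-significant test should not be read as proof that HAS adds nothing.
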